## Abstract

Supplemental Digital Content is available in the text

## Introduction

1

Functional defecation disorders include functional constipation (FC) and functional nonretentive fecal incontinence (FNRFI). FC represents a frequent reason for healthcare consultations. In a systematic review and meta-analysis that include studies using the Rome III criteria, the prevalence of FC ranged from 0.5% to 32%, with a pooled prevalence of 9.5% (95% confidence interval [CI] 7.5–12.1). For FNRFI, the prevalence ranged from 0.0% to 1.8%, with a pooled prevalence of 0.4% (95% CI 0.2–0.7).^[1]^ Additionally, the prevalence of FC was 8.6% in boys compared with 8.9% in girls (odds ratio 0.99, 95% CI 0.9–1.4). Around 3% of general pediatric outpatient visits and approximately 25% of pediatric gastroenterology consultations are related to a perceived defecation disorder, a significant proportion of which is constipation, with less than 5% of these children have an underlying organic cause.^[2,3]^ In children with FC, painful defecation, fecal incontinence, and abdominal pain may trigger emotional burdens.^[4–6]^ Also, FC is often associated with a significant impact on quality of life.^[7]^

The recommendations for diagnosis are based on history and physical examination and the Rome criteria should be used to define FC. The Rome IV criteria for children and adolescents^[8]^ and neonate and toddler,^[9]^ is a symptom-based consensus process constructed by expert clinicians centered on a literature review.^[10]^ According to the new Rome IV criteria for FC, a distinction from Rome III criteria is made for young children between those who are toilet trained and those who are not. Furthermore, the time criterion has changed, and patients now need to fulfill the criteria for at least 1 month instead of 2 months.^[11]^

In 2014, the European Society for Pediatric Gastroenterology, Hepatology, and Nutrition and the North American Society for Pediatric Gastroenterology, Hepatology, and Nutrition published a guideline that provides evidence-based recommendations for the evaluation, treatment, and follow-up of children with FC.^[3]^ The well-founded point for the treatment of FC consists of education of the child and parents, behavioral modifications, and laxative therapy.^[3,12]^ Therefore, conventional medical management of FC consists of pharmacological and nonpharmacological interventions. The pharmacological treatment of FC with laxatives involves 3 steps; disimpaction, maintenance treatment, and weaning. Nonpharmacological interventions involve education, demystification, explanation, guidance for toilet training, scheduled toilet sits, establishing a reward system, and keeping a defecation diary.^[3,13,14]^

In tertiary care centers, approximately 50% of children with FC managed with conventional treatment will be recover and taken off laxatives within 6 to 12 months, but the others, the symptoms can persist into adulthood despite intensive laxative treatment.^[15]^ Thus, a subset of patients may present with an unsatisfactory response and only minor improvement of symptoms. These children experience severe and long-lasting symptoms with recurrent fecal impactions, clinically characterized by extended intervals between defecation episodes, the passage of a large amount of stools once every 7 to 30 days and fecal incontinence that respond poorly to conventional therapy. Accordingly, when symptoms are irresponsive to optimal conventional treatment for at least 3 months, these children are considered to have intractable FC.^[3,16]^

Unfortunately, treatment options for children with constipation refractory to conventional treatment are limited. The most recent guidelines from the European and North American Pediatric Gastroenterology societies on the evaluation and treatment of FC in children recommend consideration of anal sphincter botulinum toxin injection, transanal irrigation, antegrade continence enemas, sacral nerve stimulation, and partial or total colonic resection for treatment of intractable constipation.^[3,10,17]^

Thus, neuromodulation is one of the treatment modalities that can bring benefits in patients with FC. Transcutaneous electrical stimulation (TES) is a nonpharmacological approach for children with constipation, that facilitate bowel motility, by modulating the nerves of the large bowel.^[18]^ In a systematic review, the effectiveness and safety of TES were evaluated when employed to improve constipation in children.^[19]^ The authors conclude that there are no firm conclusions regarding the efficacy of TES in children with FC, and recommended that randomized controlled trials assessing TES for the management of childhood constipation should be conducted. The future trials should include documentation of methodology and patient outcomes, such as the number of patients with improved clinical symptoms and quality of life.

On the other hand, a subtype of TES termed posterior tibial nerve stimulation (PTNS) involves electrical stimulation at the level of the ankle, delivered either percutaneously by needle punctures or transcutaneous through electrodes fixated on the overlying skin.^[20]^ PTNS transcutaneous can be considered a minimally invasive, and accessible technique with the potential to improve constipation in the pediatric population.^[20,21]^ Stimulation of the tibial nerve can modulate urinary and defecatory function through the stimulation of sacral nerves, similar to those exercised by sacral nervous stimulation (SNS). On the other hand, PTNS has the advantage of not requiring surgical procedures for the implantation of electrodes as in SNS.^[20–22]^ Multiple studies have shown that PTNS is useful for improvement of fecal incontinence in adults and treatment of several urinary dysfunctions in childhood.^[21,23,24]^

In children, only 1 study investigated the applicability of transcutaneous PTNS in a group of 8 children with fecal incontinence associated with a variety of underlying causes, including anorectal malformation, neurological conditions, and Hirschsprung disease.^[21]^ The authors found improvement of fecal incontinence after 6 months in 7 children, and 5 had a resolution of fecal incontinence. Two patients noted the recurrence of fecal incontinence with discontinuation of PTNS treatment.

Considering that there is still a need for better and more effective treatments of childhood FC and that neuromodulation has been incorporated in clinical practice for the treatment of a large number of health problems, ranging from nausea and vomiting to bowel and urinary disorders, and highlighting the potential benefits of this kind of therapy in children with FC who present symptoms refractory to clinical treatment, we decided to assess the applicability and clinical outcomes of transcutaneous PTNS in children with FC.

## Methods

2

### Study design and setting

2.1

This is a single-center, interventional, prospective, and longitudinal study design to assess the applicability and clinical outcomes of transcutaneous PTNS in children with FC. This study will be conducted at the Botucatu Medical School, São Paulo State University (UNESP), São Paulo, Brazil. The data collection period will be 12 months long, and started in April 2019.

Children will be submitted to daily sessions of transcutaneous PTNS for a period of 4 weeks. All children will also be invited to participate in semi-structured interviews, 1 in each of the 3 assessments: 1 week before the start of the intervention; immediately after the 4 weeks of intervention; and 4 weeks after the end of the intervention period. In these interviews, the aspects related to bowel habits and quality of life will be assessed.

### Ethics approval and consent to participate

2.2

This study will be conducted following the principles of the Declaration of Helsinki, ISO14155, Data Protection Act, and the Guidelines for Good Clinical Practice. The research ethics committee (REC) of the Botucatu Medical School, UNESP, São Paulo, Brazil, has approved this study, which was registered under number 80013017.0.0000.5411 (see REC, Supplemental Digital Content 1). The patients and their guardians were previously informed of the purpose of the research, and each signed an informed consent form (ICF) (see ICF, Supplemental Digital Content 2). Patients aged 11 to 18 years signed the respective specific consent form (SCF) (see SCF, Supplemental Digital Content 3). All data will be sent to the REC at the end of the study. The subjects may leave this study at any point in time without any limitations.

The Brazilian Registry of Clinical Trials (Rebec) identifier for this study is RBR-344jq8, obtained on March 13, 2018 (UTN number: U1111-1207-5487), and it is available at http://www.ensaiosclinicos.gov.br.

### Patient selection and recruitment

2.3

The estimated sample size is 28 patients, calculated for a paired *t* test (before and after intervention), based on an estimated mean increase of 7 defecations per month (according to data from previous PTNS studies^[25,26]^), an estimated standard deviation of changes = 12, a 2-tailed *α* = 0.05 and a test power *β* = 0.85. The sample will be comprised of children selected from the Pediatric Gastroenterology Outpatient and Pediatric Surgery Outpatient of the Clinics Hospital of the Botucatu Medical School -UNESP. The patients will be invited to attend an initial consultation to inform them about the study methods and apply the eligibility criteria.

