### Adherence to treatment and related adverse events

2.6

The research team members will register the treatment of patients in all the biweekly sessions of supervised PTNS and will investigate the possible occurrence of adverse events. At any point during the study, the patients/parents/guardians will be able to contact the research team by telephone to communicate possible adverse events and clarify any doubts. Patients who experience adverse effects or clinical worsening of the evacuatory pattern or who request will be discontinued from the study.

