**Figure 2 F2:**
[figure not shown]
Questionnaire addressing the evaluation of the applicability of the PTNS daily home sessions. PTNS = posterior tibial nerve stimulation.

Additionally, each patient will be monitored throughout a standardized week diary (stool frequency, stool consistency according to the mBSFS-c, frequency of fecal incontinence episodes, painful defecation, abdominal pain, blood in stools, laxative use and their doses, and adverse effects such as pain, nausea, vomiting, diarrhea, and flatulence). This diary must be filled out for 7 days, initiating 7 days before each of the assessment time points. Patients who use laxative medication will have the dosage quantity monitored, and any alterations will be registered as possible outcomes in the conclusion of the study, both in the case of increase or reduction of dosage.

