### Outcomes

2.9

Data analysis will be performed by focusing on the 3 assessment time points: assessment before the initiation of PTNS, immediately after the 4 weeks of intervention, and 4 weeks after the end of the intervention period. This analysis will be performed using the following clinical variables: number of defecations per week, number of episodes of fecal incontinence per week, need for diapers or underwear protection, need for medication for bowel habits, need for a special diet, straining and pain on defecation, presence of fecalomas, presence of abdominal pain, presence of bloody stools, need for enemas, and presence of perianal rashes or dermatitis. Also, we will analyze the results obtained by all the assessment instruments applied (mBSFS-C, BF-S, FCI questionnaire, AQLCAFI, and PEDsQL 4.0), to evaluate the outcomes of a functional status of bowel habits and the global quality of life.

As a secondary outcome, the applicability of PTNS will also be evaluated by the results of the specific questionnaire (Fig. 3), considering aspects that involve the practical difficulties for the application of this method and possible adverse events. All the situations that may be indirectly involved with the clinical results of PTNS, such as the increase or decrease of the laxative dose or any clinical or dietary changes, will also be analyzed as secondary endpoints.

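### The 85% power is worked out for defecations per month, but the variable analysed is defecations per week, recorded over 7 days

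*Protocol article*

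**What the plan says.** Section 2.3 (Patient selection and recruitment) contains the only design calculation: "The estimated sample size is 28 patients, calculated for a paired *t* test (before and after intervention"). Its inputs are a mean change "based on an estimated mean increase of 7 defecations per month", "an estimated standard deviation of changes = 12", and "a 2-tailed *α* = 0.05 and a test power *β* = 0.85". The standard deviation has no unit of its own. It stands in the same sentence as the monthly mean, so it reads as monthly. The mean is attributed to previous studies of the technique; the standard deviation is only called estimated.

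Section 2.9 (Outcomes) lists the variables to be compared across the three time points, beginning with "number of defecations per week, number of episodes of fecal incontinence per week".

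Section 2.8 (Assessment interviews), in the text after Figure 2, says that "each patient will be monitored throughout a standardized week diary (stool frequency, stool consistency according to the mBSFS-c", with further items). It fixes the window: "This diary must be filled out for 7 days, initiating 7 days before each of the assessment time points".

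**The concern.** The power statement and the analysis use different counting periods. The sample size assumes a change in a monthly count. The outcome list names a weekly count, and the only recording window in the text shown is 7 days.

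This need not be a mere matter of units. Dividing the mean by the number of weeks in a month is always legitimate. Dividing the standard deviation by the same number is legitimate only if a week tells as much about a child's change as a month does. A count over one week usually varies more, relative to its mean, than a count over four.

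At stake is how the result will be read. The Discussion (section 3) says the study is meant to show efficacy. If the paired comparison is not significant, readers will take it as the result of a study with 85% power, and that figure may not belong to the variable tested.

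**Working it through.** **Inputs from the document (section 2.3).** Mean change 7 per month; standard deviation of change 12; two-sided α = 0.05; power 0.85; n = 28.

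**Step 1: reproduce the stated figure on the monthly scale.**
- Standardised effect d = 7/12 = 0.583.
- Normal approximation: n = ((1.960 + 1.036)/0.583)² = 26.4, so 27.
- With the small-sample term z²/2 = 1.960²/2 = 1.92: n = 26.4 + 1.9 = 28.3.
- Exact noncentral t (noncentrality d√n, n − 1 degrees of freedom): power is 84.5% at n = 28 and 85.8% at n = 29.

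The stated 28 and 85% are therefore reproduced to within rounding.

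**Step 2: move to a one-week count.** Let a month hold W weeks. Assume that a child's weekly changes have equal variance s² and a common correlation ρ. The document gives no ρ. The monthly change is the sum of W weekly changes, so

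- weekly mean change = 7/W;
- 12² = W·s²·(1 + (W − 1)ρ), which gives s = 12/√(W(1 + (W − 1)ρ));
- weekly d = (7/12)·√((1 + (W − 1)ρ)/W).

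The square-root factor equals 1 only when ρ = 1. For any smaller ρ the weekly effect size is below 0.583.

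**Step 3: results for 28 children with complete data (W = 4, weekly mean change 7/4 = 1.75).**

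| Assumed ρ | Weekly SD of change | Weekly d | Exact power at n = 28 |
|---|---|---|---|
| 1 | 12/√16 = 3.00 | 0.583 | 84.5% |
| 0.8 | 12/√13.6 = 3.25 | 0.538 | 78.3% |
| 0.5 | 12/√10 = 3.79 | 0.461 | 65.3% |
| 0 | 12/√4 = 6.00 | 0.292 | 31.9% |

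**Step 4: sensitivity to the length of a month.** With a calendar month, W = 30.44/7 = 4.35 and the weekly mean change is 7/4.35 = 1.61. Power becomes 84.5%, 78.1%, 64.6% and 29.8% for the same four correlations, so the choice of month hardly matters.

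**Step 5: the case with no loss.** If the 12 was obtained by multiplying a weekly standard deviation by the number of weeks, the weekly figure is 12/4 = 3.00. Power is then 84.5%, as in the first row.

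**The case against.** The strongest reply is that per month against per week is only a change of unit. If mean and standard deviation are divided by the same factor, d and power do not move, and the stated calculation reproduces. This stands as a possibility. It is exactly right if the 12 was a weekly or rate figure scaled up, and the cited studies that might settle this are not at hand.

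A second reply is that the analysed count need not come from the diary. Section 2.9 does not name its source, and several items in its list (diapers, special diet, fecalomas, enemas, perianal rash) are not diary items. The clinical-status questionnaire in Figure 1 is not shown and may use another recall period. That also stands. Even so, section 2.9 names the variable per week, 7 days is the only window given, and nothing visible links the monthly inputs to either.

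Stronger readings are tempting, and the document does not support them:

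- **That real power is well below 85%.** A reader might infer this from the lower rows of the table. The correlation is not in the document, and the first row shows no loss. Only a range can be defended.
- **That 28 is the number enrolled and losses were overlooked.** Section 2.6 says that certain patients "will be discontinued from the study", and section 2.3 states no allowance for loss. But the text does not say whether 28 means enrolled or evaluable, nor that data from discontinued children are dropped. An article may also leave a dropout allowance to the full protocol.
- **That calling 0.85 β shows a mistaken calculation.** The same phrase calls it the test power, and the sample size reproduces with 0.85 as power. This is a slip of notation.

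**Conclusion.** The point holds as a mismatch between the scale of the power calculation and the scale of the outcome. It is not an arithmetic error. The one stated power belongs to a monthly count, and the text shown neither analyses nor describes such a count.

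For a one-week count in 28 children with complete data, power lies between about 32% and 84.5%, with 78% and 65% at intermediate correlations of 0.8 and 0.5. If the 12 came from true month-long counts, the direction is clear: power cannot exceed the monthly figure and falls below it unless weekly changes are perfectly correlated. The size of the loss cannot be fixed from the document. The range rests on an assumed common correlation and equal variance of weekly changes, and on the paired t test being the analysis.

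**What to change.** Rewrite the sample-size sentence in section 2.3 on the analysed scale:

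1. State the assumed rise per week: about 1.6 with a calendar month (7/4.35), or 1.75 with a four-week month (7/4).
2. Say whether the standard deviation of 12 came from monthly counts or from weekly counts scaled up.
3. Give the standard deviation of change for a 7-day count, or a range if it is not known.
4. Report the resulting power for 28 children with complete data, as a figure or a range, in place of 85%.

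The cost is a change of wording and possibly a less favourable stated power. Step 3 needs a figure that the document does not supply. If the earlier data cannot provide it, the range is the honest statement.

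No extra patients are needed for this correction, and the diary need not change. A longer diary would reduce noise, but before the end-of-treatment assessment it would average in earlier treatment days. Recruitment began in April 2019, so a change now would also give earlier and later children different windows.

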### Eligibility criteria

2.4

The inclusion and exclusion criteria are presented in Table 1.

**Table 1 T1:**

Eligibility criteria.

### Intervention

2.5

Patients will be submitted to transcutaneous electrical nerve stimulation of the posterior tibial nerve, based on the method described by Queralto et al (2006).^[27]^ This intervention will be supervised by a physiotherapist, who is a member of the research team with experience in this kind of therapy. A silicone auto adhesive electrode (positive electrode) will be applied approximately 3 to 4 cm above the tibial medial malleolus, and a second electrode (negative) will be placed just underneath the medial malleolus of the same leg. The electrodes will be linked to an electrical stimulation device (De Tens/Fes-2 channels, Neurodyn Portable Ibramed). The position of the electrode will be determined by visualization of rhythmic flexion of toes during stimulation. The intensity level will be determined based on the intensity immediately under the maximum sensitive threshold of the patient, usually between 10 and 25 mA. A 200-μs, 30-Hz current will be applied simultaneously in the 2 lower limbs, 30 minutes daily for 4 consecutive weeks, in the patient's home.

First, parents or guardians will be trained to perform PTNS on their children. Training sessions and supervised application will be provided until the parents feel confident enough to perform PTNS without supervision. From that point forward, PTNS will be performed daily in the household, as previously described. During the intervention period, patients should attend a supervised session of PTNS every 15 days, where the technique will be evaluated, and subsequent questions will be clarified. During this period, patients must maintain all therapeutic recommendations (drugs, diets, and behaviors) that had been previously prescribed by their referring physician. Any subsequent changes in treatment during the study period will not be avoided or delayed because of the study. Patients will be instructed to communicate with the research team about any changes in the therapeutic plan during the intervention period.

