### Intervention periods and assessment time points

2.7

The intervention period will be 4 consecutive weeks, immediately following the conclusion of the training period. The 3 time points chosen for assessment interviews will be the following: 1 week before the start of the intervention, immediately after the 4 weeks of intervention, and 4 weeks after the end of the intervention period, to identify any remaining effects of PTNS.

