### Assessment interviews

2.8

In all assessment time points, patients and/or their guardians will participate in semi-structured interviews to determine the functional results of the intervention, concerning patient bowel habits and quality of life. These interviews will be conducted by the same member of the research team and will last approximately 40 minutes. The following assessment instruments will be applied: a questionnaire addressing the current clinical status (Fig. 1); the modified Bristol Stool Form Scale for children (mBSFS-C)^[28–30]^ to analyze the stool consistency (see mBSTS-C, Supplemental Digital Content 4); the bowel function score (BF-S)^[31]^ to evaluate the functional status of bowel habits (see BF-S, Supplemental Digital Content 5); the fecal continence index (FCI) questionnaire,^[32,33]^ based on the clinical evaluation of fecal continence (see FCI, Supplemental Digital Content 6); the assessment of quality of life in children and adolescents with fecal incontinence (AQLCAFI)^[32,33]^ (see AQLCAFI, Supplemental Digital Content 7) and the pediatric quality of life inventory version 4.0 (PEDsQL 4.0)^[34,35]^ to assess the quality of life (see PEDsQL 4.0, Supplemental Digital Content 8); and a questionnaire addressing the evaluation of the applicability of the PTNS daily home sessions (Fig. 2).

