## Discussion

3

Transcutaneous PTNS has a well-established role in the treatment of children with urinary dysfunction and adults with fecal incontinence.^[20,21,25]^ There is evidence that PTNS can stimulate both the second and third sacral nerve roots, which are the same spinal segments that innervate the bladder, rectum and pelvic floor, thus modulating bowel motility and assisting in the treatment of constipation.^[26,36,37]^ On the other hand, although transcutaneous PTNS can be considered an auspicious, noninvasive and safe method to be used in the pediatric age group, there is still no published study that has investigated its use in children for the treatment of constipation.

The main objective of this study is to assess the applicability and clinical outcomes of transcutaneous PTNS in children with FC. It is intended to demonstrate the efficacy of this promising method to increase the number of complete spontaneous bowel movements, the consistency of stool, to reduce the number of episodes of retentive fecal incontinence, and improve the overall quality of life. This study is currently in the recruitment phase, which began in April 2019.

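### Applicability is rated only at scheduled interviews after home use, so families who leave in training or stop early have no described rating and the result risks being too favourable

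*Protocol article*

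**What the plan says.** All references are to the Protocol article.

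- **Entry to home use (2.5 Intervention).** "Training sessions and supervised application will be provided until the parents feel confident enough to perform PTNS without supervision". No maximum is given. Home use follows: "From that point forward, PTNS will be performed daily in the household, as previously described".
- **Start of the clock (2.7).** "The intervention period will be 4 consecutive weeks, immediately following the conclusion of the training period".
- **Interviews (2.7, 2.8).** There are three: "1 week before the start of the intervention, immediately after the 4 weeks of intervention, and 4 weeks after the end of the intervention period". The instruments applied at them include "a questionnaire addressing the evaluation of the applicability of the PTNS daily home sessions".
- **Leaving (2.6).** Adverse effects, a worse bowel pattern or a request to leave lead to discontinuation from the study itself. No exit interview is described. Treatment and adverse events are recorded at the two-weekly supervised sessions, and families may telephone at any time.
- **Status of applicability.** Section 2.9 (Outcomes): "As a secondary outcome, the applicability of PTNS will also be evaluated by the results of the specific questionnaire". The questionnaire there covers practical difficulties and possible adverse events. Discussion: "The main objective of this study is to assess the applicability and clinical outcomes of transcutaneous PTNS in children with FC".

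**The concern.** Each rule is reasonable alone, but together they tie the chance of being rated to the thing being rated. Parents who cannot master the technique do not reach home sessions. A family that finds the sessions impractical and asks to leave, or whose child has an adverse effect, exits before the week-4 interview. These are the families whose answers would be least favourable, and none has a described questionnaire rating.

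At stake is the meaning of the applicability result. It would be read as describing children with functional constipation who are offered home stimulation. If it rests only on those rated, it describes families who became confident and stayed for four weeks. For a treatment that parents deliver at home, the training effort needed and the number who never manage alone are themselves central to applicability, and the Outcomes section does not name either.

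**Working it through.** **Is there a figure to reproduce?** The article gives no applicability rate, no expected loss and no applicability denominator. Its one calculation, 28 patients for a paired t test (mean change 7, SD 12, two-sided 5%, power 0.85), concerns defecation frequency. It reproduces closely: exact power at 28 is 0.845. It matters here only for scale, since one family in 28 is 1/28 = 3.6% of the sample.

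**Who gets rated, step by step**

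| Family's course | Home sessions | Described questionnaire rating of home use |
|---|---|---|
| Leaves during training, or never confident | None | None |
| Discontinued during the 4 weeks | Some | None; perhaps treatment and adverse-event records |
| Completes the 4 weeks | All | End of week 4, and 4 weeks later |

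The list of instruments is introduced for every time point ("In all assessment time points, patients and/or their guardians will participate in semi-structured interviews"), but before the intervention there are no home sessions to rate. The end of week 4 is therefore the first informative rating. The two-weekly supervised sessions belong to the intervention period, so they come after training and do not reach families lost in it. They are not said to include the applicability questionnaire.

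**Size, as a function of unknowns.** Let *p* be the favourable rate among rated families, *f* the share of families starting training who are never rated, and *q* the favourable rate those unrated families would have given.

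- Rate over all starters = *p*(1 − *f*) + *qf*
- Overstatement = *p* − [*p*(1 − *f*) + *qf*] = *f*(*p* − *q*)

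The worst case is *q* = 0 (every unrated family counted as not applicable), giving an overstatement of *pf*. All values of *p*, *q* and *f* are assumptions.

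| *f* | All starters, *p* = 90% | Overstatement, *p* = 90% | Range for *p* = 80% to 100% |
|---|---|---|---|
| 0% | 90% | 0 points | 0 |
| 5% | 85.5% | 4.5 points | 4 to 5 |
| 10% | 81% | 9 points | 8 to 10 |
| 20% | 72% | 18 points | 16 to 20 |

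A milder assumption shrinks this in proportion. With *q* at half of *p* (45%) and *f* = 10%, the overstatement is 0.10 × (0.90 − 0.45) = 4.5 points. With *q* = *p* it is zero.

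**The case against.** The best reply is that the article excludes nobody. Training is offered as support with no pass mark, and no sentence says that families lost in training drop out of the report or the denominator. The training phase is openly described, the results are to follow CONSORT, and the flowchart and the applicability questionnaire cannot be seen in the text available. The questionnaire may ask about learning the technique. The supervised sessions check technique and record treatment and adverse events before week 4, and adverse events are one component of applicability, so early stoppers can contribute something. The analysis population may also be set out in the full protocol.

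Much of this stands, and it limits the point. A reader might infer that training is an unreported run-in, that only families completing four weeks can contribute any information, or that the result is certain to be biased upward. The documents support none of these: the phase is disclosed, partial data exist before week 4, and the bias depends on how many are lost and how they are counted.

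The reply does not supply a rating for those who leave. Whatever denominator is chosen later, a practical difficulty that was never asked about cannot be analysed. The records that do exist start after training and are described as covering treatment, technique and adverse events, which is only part of applicability.

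**Conclusion.** The point holds as a risk. Under the schedule as described, families who leave in training or are discontinued have no described applicability rating. They are plausibly the least favourable, so the questionnaire result is at risk of being too high. The size cannot be derived from the article. In the worst case, with a 90% rate among rated families, it runs from nothing if no family is lost to 18 points at 20% loss. This rests on assumed rates, on summarising applicability as a favourable/unfavourable proportion (which the article does not define), and on unrated families being left out of the reported figure.

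The conflict over status is separate and plain: the Discussion places applicability in the main objective, while the Outcomes section makes it secondary. The sections need reconciling. Overall this is a worthwhile, inexpensive improvement to the data on a stated objective, and it does not bear on the defecation-frequency sample size.

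**What to change.** 1. Give the applicability questionnaire at the point of exit, by telephone if needed, to families who leave during training or the four weeks, and record their reasons.
2. Keep a training log: sessions needed per family and the number never reaching unsupervised use. Report both as applicability results.
3. Report applicability over all families who consent and start training, showing stoppers with reasons, alongside the result in those rated. Where no answer is obtained, show the family as unrated and give the worst case as a bound.
4. Give applicability the same status in the Outcomes section and the Discussion.

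The cost is slightly more recording, using a telephone contact that already exists, and a figure that may be less favourable. No extra patients are needed, and the discontinuation rule itself need not change. Recruitment was under way when the article was written, so the exit questionnaire should start promptly: reasons not recorded when a family leaves are hard to recover.
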